#### RCT among cancer survivors

Representativeness of participants will be evaluated by comparing cancer survivors who are included in the RCT with aggregated data of all potentially eligible cancer survivors from the NCR, using students’ t-test or appropriate non-parametric tests for the following characteristics: gender, age, time of diagnosis, tumour type and stadium and treatment. Moreover, reason of non-response at baseline (from the answer card) and during the follow-up period will be tabulated to get a better understanding of the representativeness of the study sample.

Baseline sociodemographic and clinical characteristics of the intervention group and the control group will be described and compared. Primarily, all analyses will be conducted on an intention-to-treat basis. In addition, per-protocol analyses will be carried out, in which only cancer survivors who fully complete the intervention according to protocol (i.e., having completed a minimum of three sessions: an introductory session, at least one one-on-one session with an occupational therapist, and at least one session with the reintegration consultant) will be compared to the control group.

To evaluate between-group differences on the aforementioned primary and secondary outcomes, generalized estimating equations (GEE) for longitudinal data (i.e., with the primary and secondary outcomes at six (T1) and 12 months of follow-up (T2)) will be used, adjusted for baseline values of the outcome and using appropriate tests for ordered and continuous data. This approach accounts for correlated within-subject responses, allows for non-normally distributed variables and deals adequately with missing data [46–48]. If the data are not missing completely at random, non-ignorable drop-out will be adjusted for [49]. Short- (T1) and long-term (T2) effects of the intervention will be reported separately. Effect sizes will be expressed in beta, with 95% confidence interval.

The secondary outcome ‘time to RTW’ will be analysed with time-to-event analysis [50]. A Kaplan-Meier curve will be drawn, and differences between the two groups will be tested with the log rank test. In addition, the Cox proportional hazard model of survival analysis will be applied to estimate hazard ratios and the corresponding 95% confidence intervals.

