### Economic evaluation RCT

An economic evaluation will be conducted using the societal perspective, alongside the RCT, to assess the cost-effectiveness and cost-utility of the STEPS intervention compared to usual care. The costs will be evaluated with: 1) medical consumption costs (direct health care and direct non-health care costs, e.g. taxi costs obtained from the study declarations), 2) costs related to productivity loss (indirect costs) for both the intervention and the control group, and 3) the costs to deliver the intervention program. The effectiveness will be evaluated with: 1) working hours as measured in the trial (primary outcome), and 2) the utility expressed in quality of adjusted life years (QALYs) [54].

Medical consumption costs will be measured using (a selection of questions from) the iMTA’s medical consumption questionnaire for costs outside the hospital (iMCQ) (e.g., home care, informal help) [55]. Standard costs for the Netherlands [54] and prices of prescribed drugs of the Royal Dutch Society for Pharmacy [56] will be used. Costs related to productivity loss will be measured with (a selection of questions from) the iMTA’s productivity costs questionnaire (iPCQ) [55, 57]. To calculate lost productivity due to sick leave, the net number of days on sick leave will be multiplied by the estimated price of production loss of a worker per day of sick leave, based on age and gender. In case of partial sick leave, it will be assumed that cancer survivors were 100% productive during the hours of partial work resumption. The cumulative net number of days of sick leave will be converted into working hour equivalents based on a Dutch average of 1540 working hours per year, according to the Dutch guidelines [54]. To calculate these costs, the friction cost method will be used, which captures lost productivity costs only until an employee would likely be replaced by someone currently unemployed [58]. Both iMCQ and iPCQ questions will be added to the baseline (T0) and follow-up (T1 and T2) questionnaires.

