Costs to deliver the intervention will be determined by combining the training costs of the involved occupational therapists and reintegration consultants and the costs to deliver the intervention. Training costs consist of trainer costs (i.e., the expert in the preferred technique), study material costs, and attendance costs for the professionals. Costs to deliver the intervention consist of the mean hours of investment multiplied by the average wage of occupational therapists/reintegration consultant and subsequently multiplied by overhead costs. Also printing costs for the study materials will be considered. All these costs will be calculated according to the Activity Based Costing method [59], in combination with Dutch reference prices [54].

QALYs will be measured based on the utilities from the EuroQol-5D-5L [44], which will be added to the baseline and follow-up questionnaires. The Dutch tariff will be used to estimate the utility of health states described by cancer survivors. QALYs will be calculated by multiplying the utility with the amount of time a cancer survivor spend in a particular health state.

For both cost-utility (expressed in cost/QALY) and cost-effectiveness (expressed in cost/additional working hour) analyses, incremental cost-effectiveness ratios will be calculated by dividing the incremental costs by the incremental effects. The incremental cost-utility ratio indicates the additional costs needed to gain one extra QALY; the incremental cost-effectiveness ratio indicates the additional costs needed for the intervention to gain one extra unit of effect (in our case the primary outcome: additional working hour) compared to usual care. Uncertainty surrounding the input parameters will be estimated using non-parametric bootstrapping with 5000 replications [60]. The 95% confidence intervals around the mean differences will be estimated using the approximate bootstrap confidence algorithm [61]. Bootstrapped cost-effect pairs will be plotted on a cost-effectiveness plane, and a cost-effectiveness acceptability curve will be estimated applying the willingness to pay threshold [62]. The robustness of the model will be tested using various (one-way and two-way) sensitivity analyses.

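### The economic evaluation names no baseline adjustment for QALYs or costs although both are measured at T0, so the QALY difference would be less precise than the data allow

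*Protocol article*

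**What the plan says.** The protocol article, section Economic evaluation RCT, sets out the estimation chain in some detail:

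- The ratios: "incremental cost-effectiveness ratios will be calculated by dividing the incremental costs by the incremental effects".
- The uncertainty: 5000 non-parametric bootstrap replications, and "The 95% confidence intervals around the mean differences will be estimated using the approximate bootstrap confidence algorithm". A cost-effectiveness plane and an acceptability curve follow from the bootstrapped pairs.
- The QALY inputs: "QALYs will be measured based on the utilities from the EuroQol-5D-5L [44], which will be added to the baseline and follow-up questionnaires", and "QALYs will be calculated by multiplying the utility with the amount of time a cancer survivor spend in a particular health state".
- The cost inputs: "Both iMCQ and iPCQ questions will be added to the baseline (T0) and follow-up (T1 and T2) questionnaires".
- The effect in the cost-effectiveness ratio is working hours, the trial's primary outcome.

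The section mentions no regression and no baseline covariate. By contrast, the clinical analysis (Statistical analyses, RCT among cancer survivors) fits GEE models to the primary and secondary outcomes, "adjusted for baseline values of the outcome". That section also promises both unadjusted and confounder-adjusted models and refers to Table 1 for the candidate confounders. In Table 1, utility, health care consumption and productivity loss carry the code for economic evaluation variables, not the code for additional variables.

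**The concern.** T0 utility is likely to be the best single predictor of a 12-month QALY. If utility is interpolated between visits, it is also a component of that QALY. A chance difference between arms at T0 then enters the QALY difference twice: directly through its own weight, and indirectly through its correlation with utility at T1 and T2.

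Such differences are plausible here. Randomisation is stratified by recruiting hospital only, and participants range from full sick leave to fully back at work, 3 to 18 months after diagnosis. Nothing in the design balances baseline utility or baseline productivity loss.

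At stake is the precision of the cost-utility result. Cost-effectiveness is one of the article's stated hypotheses. If adjustment is left open until the data are seen, there is also room for a post-hoc choice between an adjusted and an unadjusted increment.

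**Working it through.** **The plan's own figure.** The article gives no precision figure for the economic evaluation. The RCT sample size supplies the number of completers and reproduces. With SD 13 h, effect 5.5 h, two-sided 0.05 and 80% power, n = 2 × (1.96 + 0.84)² × 13² / 5.5² ≈ 88 per arm, 176 in total. Allowing for 25% attrition, 176 / 0.75 gives 235, against the stated 236.

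**Assumptions (not in the documents).**
- Straight-line interpolation over T0, 6 and 12 months, so QALY = 0.25·U0 + 0.50·U1 + 0.25·U2.
- Equal utility variance at each visit, and correlation ρ of 0.3, 0.5 or 0.7.
- Two structures: the same ρ between all visits (compound symmetry), and correlation decaying with time (AR(1), with ρ² between T0 and T2).
- Utility SD 0.20, used only for the absolute figures.

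**Formulas, in units of the utility variance.**
- Compound symmetry: var(QALY) = 0.375 + 0.625ρ; slope on U0 = 0.25 + 0.75ρ.
- AR(1): var(QALY) = 0.375 + 0.5ρ + 0.125ρ²; slope on U0 = 0.25 + 0.5ρ + 0.25ρ².
- R² = slope² / var(QALY); adjusted SE / unadjusted SE = √(1 − R²); equivalent sample multiple = 1 / (1 − R²).

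**QALY difference.**

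| Structure | ρ | var | slope | R² | SE ratio | SE smaller by | Sample multiple |
|---|---|---|---|---|---|---|---|
| Compound symmetry | 0.3 | 0.563 | 0.475 | 0.401 | 0.774 | 23% | 1.67 |
| Compound symmetry | 0.5 | 0.688 | 0.625 | 0.568 | 0.657 | 34% | 2.32 |
| Compound symmetry | 0.7 | 0.813 | 0.775 | 0.739 | 0.511 | 49% | 3.83 |
| AR(1) | 0.3 | 0.536 | 0.423 | 0.333 | 0.817 | 18% | 1.50 |
| AR(1) | 0.5 | 0.656 | 0.562 | 0.482 | 0.720 | 28% | 1.93 |
| AR(1) | 0.7 | 0.786 | 0.722 | 0.664 | 0.580 | 42% | 2.98 |

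The percentages do not depend on the utility SD or on the number of patients.

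**Absolute size (compound symmetry, SD 0.20, 88 per arm).** The SE of the T0 utility difference is 0.20 × √(2/88) = 0.030. For ρ = 0.3, 0.5 and 0.7:
- SE of the QALY difference: 0.0226, 0.0250 and 0.0272 unadjusted; 0.0175, 0.0164 and 0.0139 adjusted.
- Expected shift of the unadjusted QALY difference from a one-SE imbalance at T0 (slope × 0.030): 0.014, 0.019 and 0.023.

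A simulation of 4,000 trials at ρ = 0.5 agrees: SE 0.0251 unadjusted and 0.0167 adjusted, with both estimators centred on the true value.

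**Costs.** With correlation r between T0 costs and follow-up costs, the SE ratio is √(1 − r²). For assumed r = 0.2, 0.3 and 0.5 this is 0.980, 0.954 and 0.866, so the SE is 2%, 5% and 13% smaller (sample multiples 1.04, 1.10 and 1.33).

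**The case against.** The strongest reply is that the section never says its differences are raw. Incremental costs, incremental effects and mean differences are all terms that fit regression-adjusted quantities, and a condensed article may leave the covariates to an analysis plan that is not shown. This stands to the extent that a reader might infer a commitment to unadjusted differences, and the text does not make one. What remains is that the chain is specified down to the interval algorithm and the number of replications, contains no covariate, and would give unadjusted increments if followed as written.

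The promise of adjusted models in the clinical section could be read as reaching the economic evaluation. Its reach is doubtful. It comes before the separate economic section, and it refers to Table 1, where utility and cost items are not coded as additional variables.

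A reader might also infer that the cost-utility result would be biased, or driven by imbalance instead of by STEPS. That goes too far. Under randomisation the unadjusted difference is unbiased, and its bootstrap interval already covers chance imbalance. The shift in the working is part of the unadjusted SE, not an error on top of it: at ρ = 0.5, 0.0188² + 0.0164² equals 0.0250² up to rounding. The problem is efficiency, and sensitivity to the imbalance that happens to occur.

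A further tempting inference is that the hours effect in the ratio would be unadjusted and so disagree with the clinical report. The documents do not support this. The economic section uses the trial's primary outcome, which the GEE adjusts for its baseline value, and no second hours effect is set up.

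**Conclusion.** The point holds as one of efficiency and specification. The economic section names no adjustment for T0 utility or T0 costs, although both are collected and the clinical analysis uses baseline values.

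For the QALY difference the loss is substantial over the assumed range: an SE 18% to 49% smaller with adjustment, equivalent to 1.5 to 3.8 times the sample. For costs the gain is modest, 2% to 13%, so a general claim of large precision loss across the economic evaluation is not supported.

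The QALY figures rest on straight-line interpolation, equal variances and correlations of 0.3 to 0.7. The cost figures rest on correlations of 0.2 to 0.5. The documents state none of these. The direction of the QALY result does not depend on the exact values, since any positive correlation between visits gives a gain.

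**What to change.** In Economic evaluation RCT, state that within each bootstrap sample:

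- the QALY increment is estimated by regression of QALYs on arm and T0 utility;
- the cost increment is estimated by regression of costs on arm and T0 costs;
- the working-hours increment is the baseline-adjusted effect defined in the clinical analysis.

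Use these increments for both ratios, the cost-effectiveness plane and the acceptability curve, and report the unadjusted differences as a sensitivity analysis. Fix this before outcome data are seen.

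The cost is a few sentences of plan text and a few lines of code. No extra data collection or patients are needed.

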	Contract type (fixed/temporary)	X			A	X	X		A
	Shift work	X			A	X	X		A
	Company size and sector	X			A	X	X		A
	Time since first day of sick leave	X			A				–
	Employment status partner (if applicable)	X			A				–
	(duration of) Caregiving leave				–	X	X		A
Work	Social support from supervisor/colleagues	X			A	X	X		A
	Job insecurity	X			A	X	X		A
	Need for recovery	X			A^c^	X	X		A
	Work accommodation	X			A^c^	X	X		A
	Impact of COVID-19 on work	X			A^c^	X	X		A
	Work attitude	X			A	X	X		A
	Self-efficacy	X			A	X	X		A
	Work-family balance	X			A^c^	X	X		A
	Work intention	X			A	X	X		A
	Fear of COVID-19	X			A	X	X		A
	Expectations regarding return to work	X			A				–
Process measures			X		P				–
Economic evaluation	Quality of life	X	X	X	E				–
	Health care consumption	X	X	X	E				
	Productivity loss	X	X	X	E				

^a^*P* Primary outcome variable, *S* Secondary outcome variable, *A* Additional variable, *M* Modifier, *E* Economic evaluation variables, *P* Process variables

^b^Only completed by participants who were on sick leave at baseline

^c^Only completed by participants who (partly) returned to work

^d^The partner will be asked regarding the medical status of the cancer survivor

**Table 2 Tab2:** List of primary, secondary and additional variables and their assessment methods

		Instrument	# items	Rating scale	Operationalization
Work outcomes	Working hours per week	Asking participants for their current number of actual working hours	1	n/a	Continuous
	Change in working hours (%)	Asking participants for their current number of actual working hours and their contractual working hours at baseline.	1	n/a	Continuous (actual working hours at follow-up as a percentage of contractual working hours at baseline).
	Employment status	Asking participants whether they are at work or not at work	1	n/a	Dichotomous
	Time to return to work	Asking participants about their first day of returning to work, from which we will estimate the number of calendar days between the first day of sick leave and the first day of work, either fulltime or part-time, for at least 28 consecutive days without recurrence.	1	n/a	Continuous
	Sick leave	Asking participants about the number of days they have been on sick leave in the past 6 months	1	n/a	Continuous

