#### RCT among cancer survivors

The primary outcome (i.e., working hours per week) will be assessed by asking cancer survivors about their current number of actual working hours. Hence, the primary outcome ranges from zero hours (for those on full sick leave) up to the number of working hours per week in the participant’s employment contract (for those fully returned to their work). This outcome was chosen as, according to the Dutch system, RTW is typically characterised by a gradual increase in work hours, while this measure is also important for workers trying to retain work. Secondary outcomes measures include: change in working hours (as a percentage of the contract hours at baseline), employment status (at work/not at work), sickness absence days, RRTW, work ability, health-related work functioning (only for cancer survivors who returned to work), time to RTW (only for cancer survivors who were on sick leave at baseline), and health-related quality of life. In addition to abovementioned outcome measures, information on a number of additional parameters (see Table 1 for a full overview) will be gathered, to describe the study sample, to include as potential confounder(s), and/or to conduct subgroup analyses.

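### The cost-effectiveness ratio divides accumulated costs by a difference in current weekly hours but is labelled as cost per additional working hour

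*Protocol article*

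**What the plan says.** All references are to the Protocol article.

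- **Primary outcome.** Under Measurements (RCT among cancer survivors), it "will be assessed by asking cancer survivors about their current number of actual working hours". Table 2 gives one item for working hours per week: "Asking participants for their current number of actual working hours". The outcome is thus a weekly rate at the time of the questionnaire, collected at T0, T1 (6 months) and T2 (12 months).
- **Effect in the economic evaluation.** Economic evaluation RCT lists it as "working hours as measured in the trial (primary outcome"), with no step that accumulates hours over time.
- **The ratio.** The same section states that "incremental cost-effectiveness ratios will be calculated by dividing the incremental costs by the incremental effects", and names the analysis "cost-effectiveness (expressed in cost/additional working hour) analyses". One unit of effect is defined by the words "gain one extra unit of effect (in our case the primary outcome: additional working hour) compared to usual care". The qualifier *per week* is missing in both places.
- **Costs.** The numerator holds care use, intervention delivery and productivity loss. The cost questions are asked at T0, T1 and T2, and sick-leave days are summed and converted to hours.
- **QALYs.** In the same section, utility is weighted by the time spent in each health state.

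**The concern.** Costs are totals over a period, and the effect is a difference between two rates at a moment. A total divided by a rate gives cost per additional weekly hour, and the text calls it cost per additional hour. The two quantities differ by however many weeks the gain lasted.

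The duration of a gain should matter in this trial. The Measurements section notes that "RTW is typically characterised by a gradual increase in work hours", and the intervention lasts at most six months, so arms may diverge at quite different points in follow-up. A difference at one visit cannot tell an early gain that was kept from one that appeared late.

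Cost-effectiveness is a stated aim, and the ratio feeds an acceptability curve, which requires a willingness to pay per unit of effect. A decision-maker would value one hour worked very differently from one extra hour every week. If the label is taken at face value, the curve is read on the wrong scale.

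**Working it through.** **1. Confirm the unit with the plan's own figure.** Sample size calculation gives SD 13 h per week, difference 5.5 h per week, power 80% and alpha 0.05; Statistical analyses makes alpha two-sided.

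n per arm = 2 × (1.960 + 0.842)² × 13² / 5.5² = 2 × 7.85 × 169 / 30.25 = 87.7, so 88 per arm, with power 0.801. With 25% attrition, 88 / 0.75 = 117.3, so 118 per arm and 236 in total. Both published figures reproduce. The 5.5 is a difference in weekly hours.

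**2. Convert a weekly difference to hours worked.** Let d0, d1 and d2 be the between-arm differences at T0, T1 and T2. Take two intervals of 26 weeks and straight-line change between visits. These are assumptions, as is d0 = 0 except in the immediate-gain row.

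Hours gained = 26 × (d0 + d1)/2 + 26 × (d1 + d2)/2

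| Path | d0, d1, d2 (h/week) | Hours gained | Hours gained / d2 |
|---|---|---|---|
| Gain only between T1 and T2 | 0, 0, 5.5 | 0 + 71.5 = 71.5 | 13 |
| Steady gain T0 to T2 | 0, 2.75, 5.5 | 35.75 + 107.25 = 143 | 26 |
| Reached at T1 and kept | 0, 5.5, 5.5 | 71.5 + 143 = 214.5 | 39 |
| Immediate and constant | 5.5, 5.5, 5.5 | 143 + 143 = 286 | 52 |
| Half of the T1 gain lost by T2 | 0, 11, 5.5 | 143 + 214.5 = 357.5 | 65 |
| T1 gain wholly lost by T2 | 0, 5.5, 0 | 71.5 + 71.5 = 143 | undefined |

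The first five rows have the same effect at T2, 5.5, although the hours gained differ fivefold (357.5 / 71.5).

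**3. Vary the time point.** The article does not say whether the T1, T2 or a pooled effect enters the ratio. With the mean of d1 and d2 as denominator, the first three paths give 71.5 / 2.75 = 26, 143 / 4.125 = 34.7 and 214.5 / 5.5 = 39.

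**4. Vary the weeks worked.** The article uses 1540 working hours per year. With an assumed 38-hour full-time week, that is 1540 / 38 = 40.5 effective weeks instead of 52. The first three factors become 10.1, 20.3 and 30.4.

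**5. Illustrate in money.** The article gives no incremental cost, so assume EUR 1,000. The planned ratio is 1000 / 5.5 = EUR 182 per unit labelled as an hour. Per hour worked it is 1000 / 71.5 = EUR 14.0, 1000 / 143 = EUR 7.0 or 1000 / 214.5 = EUR 4.7. This holds cost fixed across paths. Under the plan the cost would also differ by path, because productivity loss is in the numerator.

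**The case against.** **The unit is defined by cross-reference.** The text ties the unit to the primary outcome, which is named in hours per week elsewhere in the article. A careful reader can recover cost per additional weekly hour, and that ratio is computable. This stands. A reader might infer from step 2 that the planned figure is wrong by a factor of 13 to 39. The documents do not support that: they state no ratio, and the factor depends on an assumed path and on a T2 denominator that the text does not fix. Other paths give 52, 65 or no finite value.

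**The horizon and time point may be set elsewhere.** Twelve months of costs is implied by collection at T0, T1 and T2 but not stated, and T1 and T2 effects are to be reported separately. A condensed article may leave both details to a fuller document. Their absence alone is not the point. The unit that the article does state is.

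**Timing is partly credited through cost.** A reader might also infer that the benefit of earlier return drops out of the ratio. It does not. Sick leave is costed over follow-up, and hours of partial resumption count as fully productive, so earlier return lowers the incremental cost, within the limit set by the friction cost method. The gap is in the effect, not in the whole ratio.

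**Cumulative hours overlap with the numerator.** Hours worked are close to the complement of the sick leave already costed. This is a fair warning, but weekly hours overlap with productivity costs in the same way, so the problem exists under the current plan.

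**Cost per QALY is unaffected.** This is true, and it limits the damage. Cost per working hour remains one of the two planned ratios.

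**Conclusion.** The point holds as a mismatch of unit and duration in one of the two planned economic ratios. Accumulated costs are divided by a difference in current weekly hours, the result is named as if each unit were one hour worked, and the effect takes no account of how long a gain lasted. The plan's own handling of utility shows that a point-in-time measure needs weighting by time before it is set against accumulated cost.

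Read as the price of one hour, the ratio would be too high by roughly an order of magnitude on plausible paths. The illustrative factors of 13, 26 and 39 rest on no difference at T0, linear change, 26-week intervals and the T2 difference as denominator. They are not bounds. Read strictly as cost per additional weekly hour, the ratio can be computed and no published number is wrong. The amendment is worth making before analysis because the label determines how the acceptability curve will be read.

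**What to change.** In Economic evaluation RCT, define the effect for the cost-effectiveness analysis as cumulative hours worked from T0 to T2. This is the area under each participant's weekly-hours values at T0, T1 and T2, compared between arms with adjustment for baseline hours. State that costs cover the same horizon, and report cost per additional hour worked over that period.

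If the weekly value is kept, alone or alongside, label it *cost per additional weekly working hour at [stated time point]* and do not set it against a willingness to pay per hour.

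The cost is a change of wording and a few lines of analysis, since weekly hours are already collected at all three visits. There are two downsides. Interpolation between three visits is coarse and misses changes within each six-month interval. Hours worked also overlap with the productivity costs in the numerator. That overlap can be handled by, for example, a sensitivity analysis that leaves productivity costs out of this ratio.
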